## Abstract

**Aims::**

The purpose of the present trial is to determine whether opening co-existing chronic total occlusions (CTOs) using percutaneous coronary interventions (PCIs) improves cardiac function in patients with multi-vessel disease (MVD). Patients with MVD are defined as having at least one additional major vessel exhibiting no less than 75% stenosis combined with the presence of a CTO artery.

**Methods and results::**

Patients will be prospectively recruited who meet the following criteria:

Patients presenting with no necrosis of myocardial tissue in the territory of the CTO will be excluded. Recruited patients will be randomized into 2 groups: those undergoing PCI of only the non-CTO artery (non-CTO PCI group), and those undergoing PCI of the non-CTO artery concurrently with the CTO artery (CTO-PCI group). The primary outcome will be the change in cardiac function evaluated via CMR at a 12-month of follow-up appointment, which will be compared to a baseline measurement. Secondary outcomes include occurrence of major cardiac events, CMR-assessed myocardial viability in the CTO-supplied territory, and quality of life assessed by Seattle angina questionnaire, Patient Health Questionnaire 9 and Generalized Anxiety Disorder Scale-7 after 12-month follow-up.

**Conclusion::**

The SOS-moral trial will provide data necessary to determine whether to open concurrent CTOs among MVD patients with CMR-detected necrotic myocardial tissue.

## Introduction

1

A chronic total occlusion (CTO) is defined as a coronary artery occlusion for a period ≥3 months, which can be detected by angiogram.^[1]^ The rate of CTO detected by angiography among patients diagnosed with coronary artery disease is approximately 10% to 30%.^[1,2]^ A recent study that recruited 14,441 multi-vessel disease (MVD) patients revealed that those with a concurrent CTO lesion have higher rates of mortality than those not presenting with concurrent CTO (Hazard Risk: 1.29, *P* < .01). The difference was most significant in young patients and those with acute ST-segment elevated myocardial infarction (STEMI).^[3]^ Another study found that ischemic cardiac dysfunction was associated with increased mortality among patients with CTO lesions within the first 1 to 2 years of identification of the disease.^[4]^ Percutaneous coronary intervention (PCI) for CTO is performed to relieve symptoms, improve cardiac function, decrease the need for subsequent coronary artery bypass graft (CABG), and improve quality of life (QOL).^[5]^

Previous studies revealed that for both CTO of a single coronary artery and MVD with concurrent CTO, even with well-developed collateral circulation, successful CTO-PCI is associated with reduced long-term cardiac mortality and reduced need for CABG, which is an advantage that can persist 2 to 5 years following PCI.^[6–12]^ However, another study could not demonstrate benefits of CTO-PCI when assessing the occurrence of major adverse cardiac events (MACE); among patients with CTO of a single coronary artery, PCI did not reduce cardiac mortality and MACE when compared to optimal medical therapy (OMT).^[13]^ The prospective, open-labeled, randomized DECISION-CTO trial revealed that OMT as an initial strategy was non-inferior to PCI with regard to the composite endpoint of death, MI, stroke, or any revascularization within a 3-year follow-up period.^[14]^ A multicenter, open-labeled, randomized, controlled EuroCTO trial showed that PCI for CTO resulted in a significant improvement of health status compared with OMT alone, rather than resulting in the reduction of MACE.^[15]^

The presence of a CTO and not MVD alone has been reported to be independently associated with long-term mortality and impaired left ventricular eject fraction (LVEF).^[16]^ Hence, the effect of CTO-PCI on cardiac function merits investigation. An early study that recruited patients with at least 1 CTO and a LVEF of ≤ 40% found that CTO-PCI decreased left ventricular end-systolic volume and increased LVEF.^[17]^ Another study, with a small sample size, showed that successful CTO-PCI improved regional wall motion.^[18]^ The EXPLORE trial showed that routine CTO-PCI did not result in an overall benefit with respect to LVEF and lower left ventricular end-diastolic volume (LVEDV) within 4 months, when compared with a non-CTO PCI strategy in an unselected cohort of patients with STEMI and concurrent CTO.^[19]^ An extended examination of the EXPLORE trial also did not reveal beneficial effects associated with routine early CTO-PCI on LVEF within a 1-year period.^[20]^

Myocardial viability affects CTO-PCI outcomes. With respect to myocardial viability, the myocardium in the CTO territory can be divided into groups as follows: complete survival, partial survival, and non-viable myocardium. We predict that conflicting conclusions drawn by previous studies can be partially attributed to the failure to consider the status of myocardial tissue or the burden of ischemia.

At present, US and European guidelines provide Class IIa or IIb recommendations for PCI for the treatment of CTO. The recommendation comes despite the fact that the rate of successful CTO-PCI is more than 90% at experienced centers and can be increased by training of operators working within clinical practices, especially those in small centers. These facilities include a large portion of patients presenting with CTO combined with MVD who receive treatment involving exclusively non-CTO PCI or incomplete revascularization. The purpose of the present trial is to compare the effect of CTO-PCI combined with non-CTO PCI versus non-CTO PCI with respect to cardiac function, myocardial viability, and MACE among patients with MVD and necrotic myocardial tissue. Cardiovascular magnetic resonance (CMR) will be used to assess the viability of the myocardium, which facilitates identification of patients who will benefit from complete revascularization procedures.

## Methods

2

### Study design and randomization

2.1

This SOS-moral study is a randomized controlled trial with a multi-center design. The protocol was approved by the ethics committee of Beijing Anzhen Hospital (approval no. 2017059X) and has been registered at ClinicalTrials.gov (identifier: NCT 03372785).

Patients meeting the inclusion criteria will be categorized into two groups at a ratio of 1:1 according to a randomized digital table used to randomly assign patients to the CTO-PCI group (PCI of both the non-CTO artery and a concurrent CTO artery), or the non-CTO PCI group (PCI of only the non-CTO artery). The randomized digital form and interactive voice response mode will be applied to facilitate the randomization procedure. The randomization sequence will be produced and managed by an independent staff member. Before intervention, myocardial viability and cardiac function of patients will be evaluated using CMR. Cardiac function will be assessed using transthoracic echocardiography and CMR. The Seattle angina questionnaire (SAQ), Patient Health Questionnaire 9 and Generalized Anxiety Disorder Scale-7 will be used to evaluate patient QOL. Cardiac function, QQL, and MACE will be observed within 12 months of follow-up. A flow chart outlining the study design is depicted in Figure 1.

**Figure 1 F1:**
[figure not shown]
Flow chart of the study design. CTO = chronic total occlusion; MVD = multi-vessel disease, PCI = percutaneous coronary intervention; MACEs = major adverse cardiac events; CMR = cardiovascular magnetic resonance; QOL = quality of life; OMT = optimal medical therapy.

### Treatment groups

2.2

Patients in the CTO-PCI group receive PCI treatment involving both the CTO artery and the non-CTO artery. Patients of the non-CTO PCI group will only have PCI performed on the non-CTO artery. To ensure safety of all patients, they will be monitored, and those with persisting clinical symptoms occurring within one month of OMT will undergo PCI of CTO artery.

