### Patients and enrollment

2.3

We will enroll patients hospitalized for stable or unstable angina pectoris in Beijing Anzhen Hospital, The First Affiliated Hospital of Dalian Medical University and Beijing Friendship Hospital from April of 2018 to December of 2021 meeting the selection criteria. All subjects/guardians enrolled in the trial should clearly understand the research requirements and intervention procedures, and each will be required to sign a written informed consent agreement before participating in any type of examination or intervention. All participating research centers should obtain all informed consent forms from patients before the initiation of intervention. Personal information will be kept confidential before, during, and after the trial.

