#### Secondary endpoints

2.6.2

Secondary endpoints involve the occurrence of MACEs, defined as all-cause mortality, cardiac death, a first or recurrent, non-fatal, acute myocardial infarction, target lesion revascularization (PCI or CABG), stroke, heart failure and cardiac rehospitalization within 1, 6, and 12 months post-PCI. Other secondary endpoint will include changes in myocardial viability in the territory supplied by the CTO artery between the baseline and 12 months post-PCI, to be determined by CMR. In addition, QOL changes at 1, 6, and 12-month follow-up appointments will be assessed by comparing with baseline values using the SAQ, patient health questionnaire 9 and Generalized Anxiety Disorder Scale -7. Finally, the volume of contrast used during the procedure and the total cost of medical care covering OMT and the equipment for coronary artery disease therapy from the day of enrollment (first hospitalization) to the last follow-up (rehospitalization) will be evaluated. Perioperative myocardial infarction will be evaluated by assessing CK, CK-MB, and cTNI levels;

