### Statistical analysis

2.8

In the full analysis set, all randomized patients will be kept in the treatment group to which they were originally randomized. Moreover, patients without protocol deviation will be included in the per protocol set. Patients of the per protocol set will be included in baseline information analysis rather than in primary analysis if the CTO-PCI fails. Patients will not be included in the primary analysis if the MACEs occur.

Continuous variables normally distributed will be presented as means ± standard deviation, and student *t*-test will be used to make comparisons between two independent samples. Median and 4-quintile intervals will be used to express variables that are not normally distributed, and the Mann–Whitney *U*-test will be used to compare differences. Categorical variables will be presented as frequencies and percentages, and the differences between groups will be assessed using a chi-square test. Survival analysis will be performed using a Kaplan–Meier curve and Cox regression analysis. A 2-sided *P*-value < .05 will be considered statistically significant.

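### The 6- and 12-month angina scores compare routine with symptom-driven CTO-PCI, not CTO-PCI with none, because section 2.2 sends symptomatic controls to CTO-PCI at about one month

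*Protocol article*

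**What the plan says.** Section 2.2 (Treatment groups) defines the control strategy: "Patients of the non-CTO PCI group will only have PCI performed on the non-CTO artery". It then adds a safety rule under which "those with persisting clinical symptoms occurring within one month of OMT will undergo PCI of CTO artery". Grammatically the rule covers all patients. In practice it falls mainly on controls, whose CTO has been left closed.

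Quality of life is a secondary endpoint. The Abstract lists "quality of life assessed by Seattle angina questionnaire, Patient Health Questionnaire 9 and Generalized Anxiety Disorder Scale-7 after 12-month follow-up". Section 2.6.2 is wider: "QOL changes at 1, 6, and 12-month follow-up appointments will be assessed by comparing with baseline values using the SAQ", together with the depression and anxiety scales. Section 2.6 places the first outpatient visit at 1 month.

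Section 2.3 describes the population: "We will enroll patients hospitalized for stable or unstable angina pectoris". Section 2.8 says of the full analysis set that "all randomized patients will be kept in the treatment group to which they were originally randomized", and that "patients without protocol deviation will be included in the per protocol set". CTO-PCI given under section 2.2 is part of the protocol and is not named as a deviation. Section 4 notes that the SAQ may respond to influences other than opening the CTO. It does not mention opening the CTO in the control arm.

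**The concern.** The reason for crossing over is persisting symptoms, and symptoms are what an angina questionnaire scores. The controls who do worst on this outcome are therefore the ones offered the experimental procedure. They then contribute their later scores to the control arm. Two of the three QOL visits, including the only one named in the Abstract, come after the one-month window.

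The Abstract and section 2.1 describe the control arm as PCI of the non-CTO artery alone. By 6 and 12 months the SAQ contrast no longer matches that description. Read as CTO-PCI versus none, it leans towards no difference if the procedure works. A small or null late difference could then mean either that opening the CTO does little for symptoms, or that it helped in both arms. As written, the trial could not tell these apart. This matters because the Introduction cites a randomised trial in which CTO-PCI improved health status rather than reducing MACE, so QOL is an outcome on which benefit is plausible.

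**Working it through.** **Order of events**

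| Time | Event | Source |
|---|---|---|
| Baseline | SAQ before intervention | 2.1 |
| Within about 1 month | Persisting symptoms lead to CTO-PCI | 2.2 |
| 1 month | SAQ; order relative to that CTO-PCI not fixed | 2.6, 2.6.2 |
| 6 and 12 months | SAQ, after the crossover window | 2.6.2 |
| Analysis | As randomised | 2.8 |

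Only the 1-month score can precede the crossover, and nothing in the article secures that it does.

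**Share of the difference that remains**

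Let B be the mean SAQ benefit of successful CTO-PCI over all patients, and p the success rate. Let c be the share of controls crossing over, and r the mean benefit in those controls divided by B. Then s = c × r is the share of the total benefit that lies in them.

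- Gain in the CTO-PCI arm: p × B.
- Gain in the control arm: p × s × B.
- Difference: p × B × (1 − s), so the retained fraction is 1 − s = 1 − c × r.

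The success rate (above 80% in section 2.4.1) cancels if it is the same in both arms. The formula also assumes that later CTO-PCI yields the same benefit by the visit as initial CTO-PCI. If it yields less, more of the difference remains.

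Both c and r are assumptions. Retained fraction 1 − c × r:

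| c | r = 1 | r = 1.5 | r = 2 |
|---|---|---|---|
| 5% | 95% | 93% | 90% |
| 10% | 90% | 85% | 80% |
| 20% | 80% | 70% | 60% |
| 30% | 70% | 55% | 40% |
| 50% | 50% | 25% | 0% |

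More than half is lost only when c exceeds 0.5/r: 50% at r = 1, 33% at r = 1.5, 25% at r = 2.

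**Illustration in power**

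The plan gives no sample size or power for QOL. Section 2.7 gives 216 evaluable patients for LVEF, or 216/2 = 108 per arm. That figure reproduces with a 4-point difference, SD 9, one-sided 0.025 and 90% power by t-test, and 216/0.9 = 240 randomised. I borrow 108 per arm and assume an SAQ SD of 20 and an 8-point difference without crossover; neither value is in the documents. Two-sample t-test, two-sided 0.05:

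| s | Difference, 8 × (1 − s) | Power |
|---|---|---|
| 0 | 8 | 83% |
| 0.25 | 6 | 59% |
| 0.5 | 4 | 31% |
| 0.75 | 2 | 11% |
| 1 | 0 | 5% |

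The direction follows from the design if CTO-PCI relieves symptoms. The size depends on s.

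**The case against.** **The late contrast is valid as it stands.** Comparing immediate with symptom-driven CTO-PCI, as randomised, is a legitimate comparison of strategies. This stands, and the comparison should be kept. What does not stand is describing its control as PCI of the non-CTO artery alone.

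**The dilution may be small.** All controls first receive non-CTO PCI and medication, which may relieve their symptoms. At 5 to 10% crossover with r from 1 to 2, 80 to 95% of the difference remains. This also stands. A reader might infer that the symptom benefit is largely erased before it is measured, or that a null 12-month result is to be expected. The documents support neither: they give no crossover rate and do not show where the benefit lies. Enrolment of patients hospitalised for angina makes a material rate plausible, but no more.

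**A 1-month SAQ is already planned.** True, and it could be largely free of crossover. But section 2.2 allows CTO-PCI within that month, and the order of questionnaire and procedure is open. Making it the lead QOL result would exchange the 12-month outcome for a short-term one, so that is a trade-off and not a correction.

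**The mechanism fits only the SAQ.** Largely so. The other two scales measure depression and anxiety, which are not the trigger. Crossover can still affect them, less directly.

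**Crossover handling belongs in the analysis plan.** A condensed article may leave sensitivity analyses and crossover tables to the full documents, and their absence alone would be no fault. The point rests on what the article itself fixes: the restriction of the control arm, the rule that overrides it, the visit times and the analysis as randomised.

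**Conclusion.** The point holds in a limited form. Section 2.2 makes two statements about controls that must be reconciled. The 6- and 12-month SAQ contrasts estimate routine versus symptom-driven CTO-PCI. If the procedure relieves symptoms, they understate CTO-PCI versus none by a fraction of about s. This assumes equal success rates in both arms and full benefit of the later procedure by the time of the visit.

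The documents do not determine s. On the assumed values above, the loss runs from 5% of the difference to all of it, so no single figure should be quoted as the effect on this trial. A reader might also infer that the sponsor will report an absence of QOL benefit; no passage plans such a conclusion.

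These are secondary endpoints without stated power, which limits the weight of the point. It is worth acting on because small changes would let the trial separate an ineffective procedure from one that was also given to symptomatic controls. No view is taken on the clinical rule.

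**What to change.** Leave the clinical rule as it is, reconcile the two statements in section 2.2, and make three changes.

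1. In section 2.6.2, require the already planned 1-month SAQ to be completed before any CTO-PCI under section 2.2. If that procedure is decided before the visit, complete the questionnaire at the decision. Report this comparison alongside the 12-month result, without replacing it.
2. Keep the 6- and 12-month comparisons as randomised, but describe them as routine versus symptom-driven CTO-PCI. State that a null result will not be read as showing that CTO-PCI has no symptom benefit.
3. Report the proportion of each arm that has CTO-PCI under section 2.2. Add a sensitivity analysis of the 6- and 12-month SAQ that treats it as an unfavourable outcome, for example by worst rank or by carrying forward the score taken before that procedure.

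The cost is wording, one further analysis, and an earlier questionnaire for those patients who cross over. There are two downsides. The 1-month score shows only short-term benefit. The sensitivity analysis rests on a decision made without blinding to the arm, so it can be supportive only.

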### Experimental endpoints and procedural follow-up

2.6

Patients will be followed-up via outpatient consultation 1, 6, and 12 months following PCI. A follow-up appointment 12-months post-PCI will be conducted at the hospital. Basic characteristics including gender, BMI, waist circumference, comorbidities, medication history, blood pressure, and heart rhythm both at baseline and 1-year post-PCI will be documented by an independent physician. Blood tests assessing routine blood counts, liver and kidney function, blood lipid profiles, fasting blood glucose, glycosylated hemoglobin, hsCRP, and BNP will be recorded at baseline (before angiography) and at 1-year post-PCI. CK, CK-MB, and cTNI levels will be collected at baseline, one day after intervention, one week after intervention, and at 1-year post-PCI.

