### Sample size calculation

2.7

PASS 15.0 will be utilized to calculate sample size. In the study, 226 individuals are predicted to be recruited in the trial. This sample size was calculated using the optimal efficiency test. The main purpose of this trial is to investigate the effect successfully opening concurrent CTO lesions on cardiac function in patients with MVD. LVEF has been taken into consideration for the calculation of sample size. Previous studies revealed a 6.5% mean difference between the two experimental groups and a 9% standard deviation with respect to LVEF. The optimal boundary value for LVEF was set to 4%.^[21]^ Two-hundred sixteen cases recruited to the study will allow for the use of a 1-tailed test with a significance level (α) set to 0.025, and power (1-β) of 0.90. Ultimately, it is estimated that 240 patients will be randomized, and a 10% loss is expected to occur throughout the 1-year follow-up period.

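### Section 2.8 removes every patient with MACE from the primary LVEF analysis, and the CTO-PCI mandated in section 2.2 may make that removal uneven between arms

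*Protocol article*

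**What the plan says.** All of this is in the protocol article.

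- **Section 2.2 (Treatment groups).** For the control arm, "Patients of the non-CTO PCI group will only have PCI performed on the non-CTO artery". The safety rule follows: "those with persisting clinical symptoms occurring within one month of OMT will undergo PCI of CTO artery". It does not name an arm. Because the CTO-PCI arm has this procedure at the outset, the rule concerns mainly controls, and for them it is crossover to the experimental treatment.
- **Section 2.6 (follow-up).** "Patients will be followed-up via outpatient consultation 1, 6, and 12 months following PCI". The 12-month visit takes place at the hospital.
- **Section 2.6.2 (Secondary endpoints).** The MACE list ends with "stroke, heart failure and cardiac rehospitalization within 1, 6, and 12 months post-PCI". The rehospitalization component is not limited to unplanned admissions.
- **Section 2.8 (Statistical analysis).** In the full analysis set, "all randomized patients will be kept in the treatment group to which they were originally randomized". A later sentence takes patients with a failed CTO-PCI out of the primary analysis. The next one reads: "Patients will not be included in the primary analysis if the MACEs occur". It allows no exception, and the section never says that the full analysis set is the set for the primary analysis.

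**The concern.** MACE occurs after randomisation and can be affected by treatment. Removing patients who have it means that the primary comparison of LVEF change is no longer between the groups that were randomised. A larger sample would not repair this. The sentence also cannot be reconciled with a primary analysis on the full analysis set, so a later analysis plan would have to overrule one statement or the other.

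Section 2.2 makes the rule more awkward. A control whose symptoms persist must be given CTO-PCI. If the admission for it is classed as MACE, that control leaves the primary analysis for having been treated as the protocol requires. The number removed would then depend on symptoms after randomisation, and the route would operate mainly in one arm.

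**Working it through.** **1. The plan's own figure.** Inputs from section 2.7: SD 9, boundary 4 LVEF points, one-sided α 0.025, power 0.90. Section 2.1 gives 1:1 allocation. A two-sample t-test for a 4-point difference needs 108 per arm, 216 in total, with power 0.902. Section 2.7 adds that "a 10% loss is expected to occur throughout the 1-year follow-up period": 216 / 0.9 = 240. Both figures reproduce, with 4 points as the difference to detect.

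**2. How a control could be removed.**

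| Step | Stated? |
|---|---|
| Persisting symptoms lead to CTO-PCI | Yes, 2.2 |
| The procedure needs a new admission | No. Plausible, because follow-up is by outpatient consultation (2.6) |
| That admission counts as MACE | Not settled. Cardiac rehospitalization is unqualified (2.6.2) |
| A patient with MACE leaves the primary analysis | Yes, 2.8 |

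**3. Assumed crossover.** The documents give no rate. I take p = 5%, 10% and 20% of controls, which is 6, 12 and 24 of the 120 randomised to that arm.

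**4. Crossovers dropped: two yardsticks for the bias.**

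*Against the as-randomised analysis.* Suppose crossovers have the same prognosis as other controls and gain the full 4 points. Keeping them raises the control mean by p × 4, and dropping them removes that rise. The benefit is overstated by 0.05 × 4 = 0.2, 0.10 × 4 = 0.4 and 0.20 × 4 = 0.8 points.

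*Against a comparison in which nobody crosses over.* Suppose crossovers, left untreated, would have had a change g points worse than the retained controls. Dropping them raises the control mean by p × g, so the benefit is understated. For an assumed g of 2 to 5 points:

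- p = 5%: 0.1 to 0.25
- p = 10%: 0.2 to 0.5
- p = 20%: 0.4 to 1.0

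*Both features together.* Against the as-randomised analysis, the error is p × (4 − g). At p = 10% this is +0.2 for g = 2 and −0.1 for g = 5, so even the sign depends on g.

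For scale, the standard error of the difference is 9 × √(2/108) ≈ 1.2 points.

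**5. Power if crossovers are dropped** (difference 4, 108 against 108 × (1 − p) controls):

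- 102.6 controls: 0.894
- 97.2 controls: 0.886
- 86.4 controls: 0.865

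The loss of power is small. The problem is selection.

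**6. Power if crossovers are kept as randomised** (full effect in crossovers, difference 4 × (1 − p)):

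| p | Difference | Power |
|---|---|---|
| 0 | 4.0 | 0.902 |
| 5% | 3.8 | 0.8705 |
| 10% | 3.6 | 0.833 |
| 20% | 3.2 | 0.739 |

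If the true difference were the 6.5 points that section 2.7 quotes from previous studies, tested against zero, power would be 0.997 at 10% crossover (5.85 points), 0.988 at 20% (5.2) and 0.959 at 30% (4.55).

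**7. The other arm.** Sections 2.4.1 and 2.9 aim for a CTO-PCI success rate above 80%. Up to about 20% of 120, or 24 patients, could therefore leave the CTO-PCI arm under the failed-procedure exclusion. That is as many as the upper crossover assumption removes from controls.

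**The case against.** The strongest objection is that the route through section 2.2 needs two steps that the text does not supply: a new admission, and the classing of a planned, protocol-mandated admission as an adverse event. Section 2.9 has senior PCI experts help to identify MACE, and they might well not count it. This stands, so the route is a possibility and not a certainty.

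A reader might look for firmer support in two places, and neither provides it.

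- The cost sentence in 2.6.2 labels the last follow-up a rehospitalization, which could suggest that planned admissions count as MACE. But everyone has the 12-month visit at the hospital. On that reading every completer would have MACE and nobody would be left to analyse, so the MACE component must be narrower than the cost wording.
- Target lesion revascularization is also a MACE component. The term is not defined, and on its usual meaning a first PCI of an untreated occlusion is not one.

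It is also fair to say that the full analysis set sentence points towards analysis as randomised, and that the biases above are mostly small beside a standard error of about 1.2. But the full analysis set sentence does not cancel the MACE exclusion. It contradicts it, and the exclusion is the sentence that speaks of the primary analysis. This is a rule that the article states, not a detail that it leaves to an analysis plan.

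**Conclusion.** The point holds for the MACE exclusion itself, whatever happens under section 2.2: it selects on post-randomisation events and conflicts with the full analysis set. The mandated CTO-PCI is one conditional route by which it may remove controls unevenly.

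A reader might go further and infer that controls alone are lost, or that the trial is biased in a known direction. The documents support neither. The failed-procedure exclusion acts on the CTO-PCI arm, and the sign depends on the yardstick and on the prognosis of those removed. Under the assumptions shown (5% to 20% crossover, prognosis gap of 2 to 5 points, full 4-point gain), the crossover route alone is worth between 0.1 and 1.0 LVEF points against a 4-point target. The crossover rate and the gap are assumptions. The loss of the randomised comparison does not depend on them.

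**What to change.** Leave the clinical rule in 2.2 as it is. In 2.8:

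1. Delete the sentence that excludes patients with MACE from the primary analysis. At a minimum, state that it does not apply to patients who have the CTO-PCI mandated in 2.2.
2. Name the full analysis set as the set for the primary analysis, with all patients, crossovers included, in their randomised arm. The per-protocol comparison can remain as a supporting analysis.

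Two additions are optional: showing MACE with and without the admission for the 2.2 procedure, and a note in 2.7 that 90% power at 4 points assumes no crossover.

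The change is one of wording and needs no new visits or patients. Its statistical price is dilution of the contrast by 0.2 to 0.8 of 4 points at 5% to 20% crossover, which takes power from about 90% to between 87% and 74% if crossovers gain the full effect.
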